# PragmaTic, prospEctive, randomized, controlled, double-blind, mulTi-centre, multinational study on the safety and efficacy of a 6% HydroxYethyl Starch (HES) solution versus an electrolyte solution in trauma patients: study protocol for the TETHYS study

**DOI:** 10.1186/s13063-022-06390-x

**Published:** 2022-06-02

**Keywords:** Volume therapy, Colloids, Hydroxyethyl starch, HES, Trauma, Blood loss, Acute kidney injury

## Abstract

**Background:**

Trauma may be associated with significant to life-threatening blood loss, which in turn may increase the risk of complications and death, particularly in the absence of adequate treatment. Hydroxyethyl starch (HES) solutions are used for volume therapy to treat hypovolemia due to acute blood loss to maintain or re-establish hemodynamic stability with the ultimate goal to avoid organ hypoperfusion and cardiovascular collapse. The current study compares a 6% HES 130 solution (Volulyte 6%) versus an electrolyte solution (Ionolyte) for volume replacement therapy in adult patients with traumatic injuries, as requested by the European Medicines Agency to gain more insights into the safety and efficacy of HES in the setting of trauma care.

**Methods:**

TETHYS is a pragmatic, prospective, randomized, controlled, double-blind, multicenter, multinational trial performed in two parallel groups. Eligible consenting adults ≥ 18 years, with an estimated blood loss of ≥ 500 ml, and in whom initial surgery is deemed necessary within 24 h after blunt or penetrating trauma, will be randomized to receive intravenous treatment at an individualized dose with either a 6% HES 130, or an electrolyte solution, for a maximum of 24 h or until reaching the maximum daily dose of 30 ml/kg body weight, whatever occurs first. Sample size is estimated as 175 patients per group, 350 patients total (*α* = 0.025 one-tailed, power 1–*β* = 0.8). Composite primary endpoint evaluated in an exploratory manner will be 90-day mortality and 90-day renal failure, defined as AKIN stage ≥ 2, RIFLE injury/failure stage, or use of renal replacement therapy (RRT) during the first 3 months. Secondary efficacy and safety endpoints are fluid administration and balance, changes in vital signs and hemodynamic status, changes in laboratory parameters including renal function, coagulation, and inflammation biomarkers, incidence of adverse events during treatment period, hospital, and intensive care unit (ICU) length of stay, fitness for ICU or hospital discharge, and duration of mechanical ventilation and/or RRT.

**Discussion:**

This pragmatic study will increase the evidence on safety and efficacy of 6% HES 130 for treatment of hypovolemia secondary to acute blood loss in trauma patients.

**Trial registration:**

Registered in EudraCT, No.: 2016-002176-27 (21 April 2017) and ClinicalTrials.gov, ID: NCT03338218 (09 November 2017).

## Background

Traumatic injuries are a relevant cause of morbidity and mortality worldwide. Regardless of its nature, trauma represents a serious clinical condition, often associated with loss of vascular integrity and bleeding [1, 2]. A decrease of circulating blood volume (hypovolemia) may result in hemodynamic instability, decreased tissue perfusion, cellular hypoxia, organ damage, and finally death [3]. The aim of volume replacement therapy is to counteract hypovolemia and maintain hemodynamics, increasing oxygen delivery to tissues and restoring/preserving vital functions by matching tissue oxygen demand with supply [4, 5].

Crystalloid solutions (composed of water and electrolytes) and colloid solutions (containing macromolecules such as hydroxyethyl starch (HES), gelatin, or albumin) are routinely used for volume therapy, particularly in trauma settings with acute blood loss [6, 7]. While crystalloid solutions diffuse easily into the interstitial space, colloid solutions contain macromolecules that are less likely to pass semi-permeable biological membranes. From a physiologic point of view, this oncotic effect translates into pronounced hemodynamic effects at lower volumes, with decreased likelihood of tissue edema and complications resulting from fluid overload as compared to crystalloids [6, 8–12].

Since three investigator-initiated studies [13–15], however, reported an increased risk of renal impairment and mortality in critically ill patients, the European Medicine Agency (EMA) requested all marketing authorization holders (MAH) of HES-containing medicinal products in the European Union to develop a clinical trial strategy to provide long-term safety data of HES in the perioperative setting and trauma [16]. Accordingly, Fresenius Kabi and B. Braun Melsungen decided to perform two clinical studies to address the safety and efficacy of the use of HES: (1) the Prospective, randomized, controlled, double-blind, multi-center, multinational study on the safety and efficacy of 6% Hydroxyethyl starch (HES) sOlution versus an Electrolyte solutioN In patients undergoing eleCtive abdominal Surgery (PHOENICS) trial [17] and (2) this supportive PragmaTic, prospEctive, randomized, controlled, double-blind, mulTi-centre, multinational study on the safety and efficacy of a 6% HydroxYethyl Starch (HES) solution versus an electrolyte solution in trauma patients (TETHYS).

### Study objective

The primary objective of this study is to evaluate the safety of a 6% HES 130 solution compared to an electrolyte solution for infusion in patients with trauma, using an exploratory non-inferiority design. Secondary objectives are to further assess efficacy and safety, as determined by renal function, blood coagulation, inflammation, hemodynamics, total administered investigational product (IP) volume over the study time, fluid balance, concomitant medication, need of blood products, (serious) adverse events, and additional outcome parameters.

## Methods/design

### Trial design

TETHYS is a pragmatic, prospective, randomized, controlled, double-blind, multi-center, multinational study, performed in two parallel groups of patients admitted to general hospitals, and allocated in a 1:1 fashion to receive either a 6% HES 130 solution (Volulyte® 6%, Fresenius Kabi Deutschland GmbH, Bad Homburg, Germany; HES group) or an electrolyte solution (Ionolyte®, Fresenius Kabi Deutschland GmbH, Bad Homburg, Germany; control group). The study is conducted as a phase IV study in most European countries of conduct; in Serbia, Czech Republic, and South Africa, it is a phase III study. Independent ethical committee (IEC) approval to the corresponding protocol versions has been already granted in most of the participants’ countries. The corresponding study protocols are described in this publication in accordance with the SPIRIT Guidelines [18].

### Participants

The study is conducted in a population of adult (≥18 years of age) patients, both genders, presenting with blunt or penetrating trauma, an estimated blood loss of ≥ 500 ml, an indication of surgery within 24 h after trauma, and no signs of intracranial or cerebral hemorrhage. Eligible patients must consent to participate in the trial, either personally, or following a deferred written informed consent, or as locally required. Patients must not have received ≥ 15 ml/kg body weight of colloids between trauma injury and hospital admission. Females of childbearing potential must test negative on a standard pregnancy test to participate in the study. Patients are also excluded from the trial if meeting any of the following criteria: known or suspected hypersensitivity to any of the investigational product or its excipients, body weight of ≥ 140 kg, expectancy of death within 24 h after traumatic injury, sepsis, burns, renal and impairment at time of admission (defined as AKIN stage ≥ 1, or chronic kidney failure). The same is true for patients receiving acute or chronic renal replacement therapy (RRT), critically ill patients (typically admitted to the intensive care unit, ICU), or patients suffering from hyperhydration, pulmonary edema, dehydration, hyperkalemia, severe hypernatremia, severe hyperchloremia, severely impaired hepatic function, congestive heart failure, severe coagulopathy, organ transplant patients, and metabolic alkalosis. Trial participation is also excluded for patients with simultaneous participation in another interventional clinical trial for either drugs or medical devices.

In line with the scientific advice obtained from the EMA Scientific Advice Working Party, it is aimed to recruit as many patients as possible (up to 350 patients) within the recruitment period of the concurrent perioperative study PHOENICS [17]. A list of the participating sites in TETHYS can be found at Clinicaltrials.gov (NCT03338218).

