### Study phases and interventions

A detailed schematic of all study procedures is shown in Table 1.

**Table 1 Tab1:** TETHYS study flow diagram

	Time					
	Screening: at hospital admission	T0 (baseline): emergency room until IP treatment start	T1: First 24 h after IP treatment start^b^	T2: post-traumatic day 1^b^-3 (morning)	T3: post-traumatic day 4-7 (morning)	T4^c^: day 90 after randomization

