**Procedure**						
Inclusion/exclusion criteria	X					
Randomization		X				
Demographic data and medical history	X					
Anamnesis and concomitant diseases (only ongoing and relevant resolved)	X					
Date and time of hospital admission	X					
Blunt/penetrating trauma	X					
Injury characteristics	X					
Fluid input (colloids, crystalloids) after trauma injury and until hospital admission	X					
Surgery due to traumatic injury						
• Type of surgery • Date • Time of skin incision/time of skin suture			X	X	X	
SCr [mg/dl] SCr-based eGFR [ml/min] Cystatin-C [mg/dl] Cystatin-C based eGFR [ml/min] Cystatin-C-based mean eGFR [ml/min] (calculated from the highest cystatin-C level during days 1–3) AKIN score (calculated) Highest AKIN stage reached on each day (during the first week) (calculated) RIFLE score (calculated) Urine output (if available)		X	X^a^	X	X^d^	
C-reactive protein [mg/L]		X	X^a^	X		
Platelet count [μ/L] INR aPTT [s]		X	X^a^	X		
pCO_2_ [mmHg] pO_2_ [mmHg] HCO_3_^-^ [mmol/l] SaO_2_ [%] pH Base excess [mEq/l] Hb [g/dl] Hct [%] Lactate [mmol/l]		X	X^a^	X		
ScvO_2_ [%] (if available)		X	X^a^	X		
Na^+^ [mmol/l] K^+^ [mmol/l] Ca^2+^ [mmol/l] Cl^-^ [mmol/l]		X	X^a^	X		
Administered IP volume [19]		X	X			
Fluid input [19] (incl. every i.v. medication, applied blood products) Fluid output [19] (incl. drainage, urine output, estimated blood loss)		X	X	X	X	
Temperature [°C]		X	X	X	X	
MAP [mmHg] (calculated) HR [beats/min] SAP [mmHg] DAP [mmHg] CVP [mmHg] (if available)		X	X^a^	X	X	
Hemodynamics as required to determine volume responsiveness (one variable if applicable)						
• MAP [mmHg] • SV [19] • SVV [%] • PPV [%] • SVI [ml/min^2^]		During duration of IP administration to assess volume responsiveness				
Mechanical ventilation	X	X	X	X	X	
Use of RRT			X	X	X	X
Antibiotics Contrast agents Diuretics		X	X	X	X	
Crystalloid (including basal infusion)/albumin						
• Administered drug • Volume		X	X	X	X	
Vasoactive/inotropic drugs						
• Administered drug • Dosage/volume		X	X	X	X	
Fibrinogen/PCC/factor XIII						
• Administered drug • Dosage/volume		X	X	X	X	
Applied blood products [19]						
• Administered drug • Dosage/volume		X	X	X	X	
(Serious) adverse events		continuously				
Date and time of hospital discharge					At hospital discharge	
Fulfilment of fit for discharge criteria from hospital					Daily until fulfilment	X
Date of ICU admission		At ICU admission				
Date and time of discharge from ICU				At ICU discharge		

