**Fig. 3 Fig3:**
[figure not shown]
Stroke volume variation optimization protocol to guide perioperative volume losses. VV, stroke volume variation; MAP, mean arterial pressure; IP, investigational product (Volulyte or Ionolyte)

Treatment with IP is provided until a maximum of 24 h after start of its administration, or until reaching a maximum daily dose of 30 mL/kg, whatever occurs first. In case the patient is still hypotensive during IP administration, vasoactive/inotropic drugs can be administered, if considered necessary. As HES preparations for volume replacement rarely cause allergic reactions of varying severity, the first 10-20 ml of IP are infused slowly. In case of an allergic reaction, the infusion is stopped immediately, and appropriate treatment is to be initiated.

In case the patient is not hemodynamically stabilized after having received the maximum allowed daily IP dosage of 30 ml/kg or 24 h after IP treatment start (whatever occurs first), only crystalloid solutions, or albumin are to be administered. The choice of the solution is at the discretion of the treating physician and shall be documented in the electronic case report form (eCRF), including administered volume. If needed, blood products can be given throughout the study period and should be transfused in accordance with current ESAIC guideline [20], recommending a target hemoglobin concentration of 7-9 g/dl during active bleeding, or, in South African sites, according to the current version of the Clinical Guidelines for the Use of Blood Products in South Africa by the South African National Blood Transfusion Service [21], which recommend administration of red blood cell component (RBC) if the acute blood loss is greater than 30% of blood volume, until reaching a preoperatory target hemoglobin concentration between 7 and 10 g/dl; RBC transfusions above 10 g/dL are not recommended.

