### Concomitant medication

#### Allowed concomitant medication

The following medications are allowed, as long as they are provided solely via a separate infusion system, independently from the IP infusion system:Vasoactive/inotropic treatment, starting earliest after third IP volume challenge or if clinically deemed necessaryMedication that is clinically required, except other volume replacement therapy (either colloids or crystalloids) during IP treatment period, e.g., antibiotics or pain medicationCrystalloid solutions or albumin, if clinically required, after treatment phase, i.e., after achieving the maximum daily dose of 30 ml/kg IP or maximum IP treatment period of 24 h, whatever occurs firstIf concomitant blood products are necessary, these should only be given according to the most current version of either the ESAIC guideline on the management of severe perioperative bleeding [20], or the Clinical Guidelines for the Use of Blood Products in South Africa by the South African National Blood Transfusion Service [21], wherever applicable

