#### Secondary outcomes

The assessment of secondary variables (listed in Table 2) will provide further information on safety and efficacy of both IPs. Date and time of assessment are documented for all variables.

**Table 2 Tab2:** Secondary variables

Safety parameters	Efficacy parameters	Other variables

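### As the article words it, the 30 ml/kg ceiling counts only investigational product, so HES given beforehand can take a compliant HES-arm patient above 30 ml/kg of HES in 24 h

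*Protocol article*

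**What the plan says.** - **Entry (Participants):** "Patients must not have received ≥ 15 ml/kg body weight of colloids between trauma injury and hospital admission". Anything below that amount is allowed, and the limit stops at admission.
- **HES is a colloid (Background):** the article describes "colloid solutions (containing macromolecules such as hydroxyethyl starch (HES), gelatin, or albumin", and the list of prohibited concomitant medication also names other HES solutions among the colloids.
- **Clock (Treatment phase):** "Treatment with IP is provided until a maximum of 24 h after start of its administration", or until the 30 ml/kg maximum daily dose is reached, if sooner.
- **What the ceiling counts:** the Treatment phase section describes a patient "after having received the maximum allowed daily IP dosage of 30 ml/kg", and Allowed concomitant medication speaks of "after achieving the maximum daily dose of 30 ml/kg IP". Both tie the ceiling to IP.
- **Other colloids (Not allowed concomitant medication):** all are barred during the IP phase, and synthetic ones from then until discharge. Neither ban reaches back before IP start.
- **Records (Table 1; Secondary outcomes):** there is a screening row for "Fluid input (colloids, crystalloids) after trauma injury and until hospital admission". A separate fluid-input row, which includes intravenous medication, is marked for the period "T0 (baseline): emergency room until IP treatment start". In addition, "Date and time of assessment are documented for all variables".

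**The concern.** The article closes off additional HES during IP treatment and, until discharge, after it. It also treats prior colloid as relevant by setting an exclusion threshold. The threshold and the ceiling are not connected, however: HES given before IP takes nothing off the 30 ml/kg.

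The trial exists to study the safety of HES, and its primary outcome combines death and renal failure. Under the rule as printed, a patient treated exactly to protocol could receive more HES in 24 h than the trial allows as IP. That extra exposure is avoidable. For such a patient, IP volume taken alone would also understate the HES received.

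**Working it through.** There is no computed figure to reproduce, because the ceiling is a rule. The sample size of 175 per group plays no part.

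**Inputs from the article:** prior colloid below 15 ml/kg before admission; IP up to 30 ml/kg over at most 24 h from its own start.

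**Inputs not in the article, so varied:** x, the HES given before IP (ml/kg), taken as one dose; t, the hours from that dose to IP start; D, the hours over which 30 ml/kg of IP is given at an even rate.

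**Step 1, total over the whole episode.** Total HES = x + 30, and the total passes 30 once IP exceeds 30 − x.

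**Step 2, highest total in any 24 h.** The IP falling in the 24 h that open with the prior dose is 30 × min(1, (24 − t)/D). The highest 24 h total is the larger of 30 and x plus that amount.

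- D = 24 (slowest case): x + 30 − 1.25t, which is above 30 only if t < x/1.25.
- D = 12: above 30 only if t < 24 − 12(30 − x)/30.
- D = 6: above 30 only if t < 24 − 6(30 − x)/30.

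| x (ml/kg) | Total HES at full IP | IP at which total passes 30 | 24 h total, t = 2 h, D = 24 | Exceeds 30 in 24 h if t is under: D = 24 | D = 12 | D = 6 |
|---|---|---|---|---|---|---|
| 5 | 35 | 25 | 32.5 | 4 h | 14 h | 19 h |
| 10 | 40 | 20 | 37.5 | 8 h | 16 h | 20 h |
| 15 (limit, not reached) | 45 | 15 | 42.5 | 12 h | 18 h | 21 h |

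Relative to 30 ml/kg, the whole-episode totals are 17%, 33% and just under 50% higher. Emergency-room HES would add to x, and the article states no limit for it.

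**Step 3, example.** Assume 80 kg and 500 ml of prior HES, so x = 500/80 = 6.25. The total passes 30 ml/kg after (30 − 6.25) × 80 = 1,900 ml of IP. With an even 24 h infusion this falls within 24 h of the prior dose only if t < 6.25/1.25 = 5 h.

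**The case against.** **The article is condensed.** A deduction for earlier HES may stand in the full protocol or in the dosing figures, neither of which is shown. This stands, and the fix is conditional on it. The point is still more than a missing detail, because the article does state the ceiling, twice, in words that count IP only.

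**Other wording points the other way.** The abstract and one sentence in the Treatment phase section give the 30 ml/kg maximum without the word IP, which could be read as total HES. The Discussion says that approved dosing is respected. Neither tells a site how to count earlier HES, and two possible readings are themselves a reason to clarify.

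**No benchmark for harm.** A reader might infer that approved dosing is breached. The article gives neither the approved limit nor how it treats earlier HES, so that inference is not supported. The only yardstick here is the trial's own IP ceiling.

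**Bias.** A reader might also infer that the treatment comparison is distorted. It is not: prior HES precedes IP, and 1:1 randomisation should balance it between arms.

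**Data.** Pre-admission fluids and fluid input up to IP start are already recorded, with dates and times. This stands too. Much of what is needed for a total-HES figure probably exists; the article does not show whether colloid type is captured.

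**Stacked conditions.** The prior colloid must be HES rather than gelatin or albumin, the patient must be in the HES arm, IP must exceed 30 − x, and the timing must fit. Critically ill patients are excluded and dosing follows need, so few patients may qualify.

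**Conclusion.** The point holds for the article's wording, as a low-cost patient-safety improvement. A compliant HES-arm patient can exceed 30 ml/kg of HES in 24 h. Total HES is bounded just under 45 ml/kg, plus any HES given in the emergency room. The 35, 40 and 45 ml/kg figures are whole-episode totals. They fall within 24 h only when the interval to IP start is short enough: under 4 h, 8 h and about 12 h respectively for any excess at all in the slowest infusion case, and longer with faster infusion.

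The result assumes a single prior dose, even infusion and the full 30 ml/kg of IP. The frequency is unknown, because the article gives neither the share of patients with prior HES nor the interval to IP start. It does not show a breach of approved dosing or a biased comparison between arms.

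**What to change.** Unless the full protocol already does so, state in Treatment phase and in Allowed concomitant medication that HES given in the 24 h before IP start is deducted from the 30 ml/kg IP ceiling. For example, 10 ml/kg of prior HES leaves 20 ml/kg of IP. Apply this identically in both arms, which keeps the blind, with crystalloid or albumin afterwards as already allowed.

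Report total HES (prior plus IP) by arm, using the pre-admission and baseline fluid records already collected. Add a field for colloid type only if it is not captured. For enrolled patients whose colloid type is unknown, report an upper bound that treats all prior colloid as HES given in the same 24 h as the IP.

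**Cost:** one amendment sentence, one derived variable and possibly one data field. Patients with prior HES may receive slightly less IP, which marginally reduces the dose contrast and so leans towards non-inferiority. If a share p had prior HES of x and all would otherwise reach the ceiling, mean IP falls by at most p × x. With assumed values, 0.10 × 5 = 0.5 ml/kg (0.5/30 = 1.7%) and 0.20 × 10 = 2 ml/kg (2/30 = 6.7%). The sample size is unchanged.

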### Investigational products (IPs)

The investigational test product Volulyte® 6% is a clear to slightly opalescent, colorless 6% HES 130/0.4 solution in an isotonic, balanced electrolyte solution. The investigational reference product Ionolyte® is a clear and colorless, aqueous, balanced electrolyte solution. Since Ionolyte® has the identical electrolyte composition as Volulyte® 6%, it is the most suitable comparator. Both products are solutions for infusion provided in 500 ml polyolefin bag (Freeflex®) with overwrap.

### Study phases and interventions

A detailed schematic of all study procedures is shown in Table 1.

**Table 1 Tab1:** TETHYS study flow diagram

	Time					
	Screening: at hospital admission	T0 (baseline): emergency room until IP treatment start	T1: First 24 h after IP treatment start^b^	T2: post-traumatic day 1^b^-3 (morning)	T3: post-traumatic day 4-7 (morning)	T4^c^: day 90 after randomization
**Procedure**						
Inclusion/exclusion criteria	X					
Randomization		X				
Demographic data and medical history	X					
Anamnesis and concomitant diseases (only ongoing and relevant resolved)	X					
Date and time of hospital admission	X					
Blunt/penetrating trauma	X					
Injury characteristics	X					
Fluid input (colloids, crystalloids) after trauma injury and until hospital admission	X					
Surgery due to traumatic injury						
• Type of surgery • Date • Time of skin incision/time of skin suture			X	X	X	
SCr [mg/dl] SCr-based eGFR [ml/min] Cystatin-C [mg/dl] Cystatin-C based eGFR [ml/min] Cystatin-C-based mean eGFR [ml/min] (calculated from the highest cystatin-C level during days 1–3) AKIN score (calculated) Highest AKIN stage reached on each day (during the first week) (calculated) RIFLE score (calculated) Urine output (if available)		X	X^a^	X	X^d^	
C-reactive protein [mg/L]		X	X^a^	X		
Platelet count [μ/L] INR aPTT [s]		X	X^a^	X		
pCO_2_ [mmHg] pO_2_ [mmHg] HCO_3_^-^ [mmol/l] SaO_2_ [%] pH Base excess [mEq/l] Hb [g/dl] Hct [%] Lactate [mmol/l]		X	X^a^	X		
ScvO_2_ [%] (if available)		X	X^a^	X		
Na^+^ [mmol/l] K^+^ [mmol/l] Ca^2+^ [mmol/l] Cl^-^ [mmol/l]		X	X^a^	X		
Administered IP volume [19]		X	X			
Fluid input [19] (incl. every i.v. medication, applied blood products) Fluid output [19] (incl. drainage, urine output, estimated blood loss)		X	X	X	X	
Temperature [°C]		X	X	X	X	
MAP [mmHg] (calculated) HR [beats/min] SAP [mmHg] DAP [mmHg] CVP [mmHg] (if available)		X	X^a^	X	X	
Hemodynamics as required to determine volume responsiveness (one variable if applicable)						
• MAP [mmHg] • SV [19] • SVV [%] • PPV [%] • SVI [ml/min^2^]		During duration of IP administration to assess volume responsiveness				
Mechanical ventilation	X	X	X	X	X	
Use of RRT			X	X	X	X
Antibiotics Contrast agents Diuretics		X	X	X	X	
Crystalloid (including basal infusion)/albumin						
• Administered drug • Volume		X	X	X	X	
Vasoactive/inotropic drugs						
• Administered drug • Dosage/volume		X	X	X	X	
Fibrinogen/PCC/factor XIII						
• Administered drug • Dosage/volume		X	X	X	X	
Applied blood products [19]						
• Administered drug • Dosage/volume		X	X	X	X	
(Serious) adverse events		continuously				
Date and time of hospital discharge					At hospital discharge	
Fulfilment of fit for discharge criteria from hospital					Daily until fulfilment	X
Date of ICU admission		At ICU admission				
Date and time of discharge from ICU				At ICU discharge		
Fulfilment of fit for ICU discharge criteria				Daily until fulfilment		X
Mortality (in-hospital/out of hospital)				X	X	X
Study termination		At termination				

^a^At least every 6 h

^b^In case assessment of time points T1 and T2 (day 1) are within a timespan of max. 2 h only one assessment per variable has to be done to minimize intervention for the patient, otherwise deemed clinically required

^c^A lag time of ± 14 days for the conduct of this follow-up contact is accepted, to account difficulties in obtaining data due to potential causes for delay (e.g., mail delay, or patient´s inability to travel)

^d^except cystatin-C

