#### Study assessments and follow-up

Study data are collected at different time points during the study, from baseline (after hospital admission, at emergency room until IP treatment start), up to 7 days after trauma, followed by a period of 90 ± 14 days after randomization. A detailed schematic showing the time points for study assessments and procedures, including follow-up, is presented in Table 1.

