### Outcomes

#### Primary outcome

The primary outcome is a composite of 90-day mortality and 90-day renal failure, defined by biomarker increase according to AKIN [22] stage ≥ 2, RIFLE [23] injury or failure stage, or need for RRT including hemodialysis, peritoneal dialysis, hemofiltration, and renal transplantation at any time during the first 3 months after treatment with IP.

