#### Sample size

Only descriptive statistics and explorative analyses will be performed, since this study is designed as pragmatic, and supportive to the PHOENICS [17]. Nonetheless, a power analysis was performed.

The composite endpoint of 90-day mortality and 90-day renal failure serves as primary variable. The rate of events of interest is unknown, therefore we defined 50% as a statistically unfavorable condition. Using a non-inferiority margin of *δ* = 15%, both the null hypothesis (*H*_0_, *E*_*T*_ ≥ *E*_*S*_ + 15%) and the alternative hypothesis (*H*_*A*_, *E*_*T*_ < *E*_*S*_ + 15%), where *E*_*T*_ and *E*_*S*_ denote the event rate for the primary endpoint upon Volulyte® 6% and Ionolyte, respectively, will need to be tested on the level of *α* = 0.025 (one-tailed). Therefore, and based on these assumptions, the sample size estimation results in 175 patients per group, 350 patients in total (*α* = 0.025 one-tailed, power 1–*β* = 0.8; SAS PROC POWER). This is considered as the maximum sample size. Power calculations were performed for different sample sizes, up to a power 1–*β* = 0.6, for which a sample size of 109 patients per group, i.e., 218 patients in total, was therefore determined as the minimum acceptable to provide supportive results. The non-inferiority margin of 15% was chosen based on feasibility aspects, in alignment with the competent regulatory authorities, and, particularly, considering the timelines they set for the duration of two concurrent trials in different populations: this trial, and the concurrent PHOENICS [17].

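### The T4 window opens at day 76, so a contact that complies with the protocol can leave up to 14 days of the 90-day primary endpoint unobserved

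*Protocol article*

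**What the plan says.** - **Endpoint (Outcomes, Primary outcome).** "The primary outcome is a composite of 90-day mortality and 90-day renal failure". RRT counts if needed "at any time during the first 3 months after treatment with IP". The abstract's Methods gives the same period without an origin: "use of renal replacement therapy (RRT) during the first 3 months".
- **Visit (Table 1).** T4 is set at "day 90 after randomization". Footnote c adds: "A lag time of ± 14 days for the conduct of this follow-up contact is accepted". Its stated purpose is "to account difficulties in obtaining data due to potential causes for delay", with postal delay and a patient being unable to travel as the examples.
- **Text (Study assessments and follow-up).** The window is repeated: data collection up to 7 days after trauma is "followed by a period of 90 ± 14 days after randomization".
- **What is collected when (Table 1).** RRT use is scheduled at T1 to T4 and mortality at T2 to T4. T3 covers post-traumatic days 4 to 7, and nothing is scheduled for either item between T3 and T4. Creatinine, AKIN and RIFLE end at T3. (Serious) adverse events are recorded continuously.

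**The concern.** An endpoint fixed at 90 days needs every surviving patient's status to be known through day 90. The window is symmetric, so a site can complete T4 on day 76 and have followed the protocol in full. For that patient the last two weeks of the endpoint period are covered only by adverse event reporting.

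The early half of the window also lacks a reason. Footnote c describes a lag and lists causes of delay. These explain a contact after day 90 and cannot explain one before it.

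The two halves differ in whether they can be repaired later. After a late contact, events beyond day 90 can be removed by date. After an early contact, events that were never collected cannot be recovered by any analysis rule; they can only be imputed or treated as censored. The trial tests non-inferiority on a safety endpoint, and losing events from both arms tends to pull the absolute difference towards zero, which is the lenient direction.

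**Working it through.** **1. Window.** Inputs: day 90 (Table 1) and ± 14 days (footnote c; Study assessments and follow-up). Earliest compliant contact: 90 − 14 = day 76. Latest: 90 + 14 = day 104. Largest unobserved part of the endpoint period: 14/90 = 15.6%.

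**2. Which components are exposed.** AKIN and RIFLE events rest on creatinine scheduled to day 7, so an early T4 cannot lose them. Only deaths and first RRT on days 76 to 90 are at risk, and only in patients contacted early.

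**3. The plan's sample size.** Inputs from Sample size: 50% event rate, margin 15 points, one-sided α = 0.025. With unpooled variance, n per group = (z₁₋α + z₁₋β)² × [p(1−p) + p(1−p)] / δ².
- Power 0.80: (1.960 + 0.842)² × 0.5 / 0.0225, rounded up to 175. The stated figure is reproduced.
- Power 0.60: (1.960 + 0.253)² × 0.5 / 0.0225, rounded up to 109. The stated minimum is reproduced.

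The formula has no follow-up term, so changing the window leaves both figures as they are.

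**4. Loss in the event rate.** The article gives neither event timing nor the share of early contacts, so these are assumed ranges. Let p be the 90-day event rate, s the share of those events falling on days 76 to 90, and f the share of patients contacted on day 76. Points lost = 100 × p × s × f; events lost among 350 = 350 × p × s × f. The 50% rate is the plan's planning value, taken because the true rate is unknown ("therefore we defined 50% as a statistically unfavorable condition"); 20% is shown for comparison.

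| p | s | f = 25%: points (events) | f = 100%: points (events) |
|---|---|---|---|
| 50% | 1% | 0.12 (0.4) | 0.50 (1.75) |
| 50% | 5% | 0.62 (2.2) | 2.50 (8.75) |
| 50% | 15.6% | 1.94 (6.8) | 7.78 (27.2) |
| 20% | 1% | 0.05 (0.2) | 0.20 (0.7) |
| 20% | 5% | 0.25 (0.9) | 1.00 (3.5) |
| 20% | 15.6% | 0.78 (2.7) | 3.11 (10.9) |

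The 15.6% rows spread all events evenly over 90 days. They are an upper bound that does not fit step 2.

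**5. Loss in the risk difference.** Suppose both arms lose the same share and the true difference sits at the margin (50% against 65%). The observed difference is then 15 × (1 − s × f) points. It falls by less than 1 point whenever s × f is below 1/15 = 6.7%.

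For f = 100% and 175 per group, the one-sided type I error is 1 − Φ(1.960 − 0.15s/SE), where SE is computed from the reduced rates 0.65(1−s) and 0.50(1−s).

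| s | observed difference (points) | type I error (nominal 0.025) |
|---|---|---|
| 1% | 14.85 | 0.027 |
| 5% | 14.25 | 0.035 |
| 15.6% | 12.67 | 0.064 |

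Equal proportional loss is itself an assumption. Late events concentrated in one arm would alter the size of the effect and could alter its direction.

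**6. Time origin.** T4 counts from randomization. The RRT part of the endpoint counts from treatment with IP. No origin is given for 90-day mortality. Table 1 places randomization in T0, which ends when IP treatment starts, so the gap is probably short.

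**The case against.** The strongest reply is that footnote c governs when a contact may take place, while the endpoint period is fixed separately under Primary outcome. Much of this stands, and it rules out several stronger readings that a reader might infer.

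- **That events on days 91 to 104 would be counted.** The endpoint is limited to 90 days or 3 months. Secondary outcomes says that date and time of assessment are documented for all variables, and Statistical methods plans Kaplan-Meier and Cox analyses for secondary outcomes, which need event dates. Nothing suggests that later events would enter.
- **That a patient contacted on day 76 is scored event-free.** The article states no such rule. Classifying incomplete 90-day observation is ordinary SAP content, and its absence here is no fault.
- **That T4 is the only source of information after day 7.** It is the only scheduled collection of mortality and RRT. Continuous adverse event reporting, discharge tracking and the required efforts to reach patients who miss a visit may capture some late events.
- **That the type I error rises to 0.064.** This needs every patient contacted on day 76 and events spread evenly, which the day-7 creatinine schedule contradicts.
- **That the two time origins distort the result.** The probable gap is a small fraction of 90 days.

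It can also be said that the analysis is exploratory and supportive, and that an amendment in a running multinational trial is not trivial. Both are true and limit the weight of the point. None of this answers the core: the early side of the window is allowed, no reason is given for it, and what it loses cannot be restored at analysis.

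**Conclusion.** The point holds as a small, avoidable weakness in the early half of the T4 window. A compliant contact on days 76 to 89 leaves part of the primary endpoint period without scheduled observation, at most 14 of 90 days. The effect on the risk difference is probably under 1 percentage point against a 15-point margin. That judgement assumes that few composite events are late first events and that not all patients are contacted early; the article has no data on either. Early contact is permitted, not certain. If the two arms lose similar shares of events, the bias favours non-inferiority, which is why even a small loss is worth preventing. The time-origin mismatch is a wording matter.

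**What to change.** 1. In Table 1 footnote c and in Study assessments and follow-up, make the window one-sided: T4 not before day 90 and up to 14 days later (day 90 to day 104). The footnote's own reasons then fit the rule.
2. State that the primary endpoint is classified by deaths and renal events dated on or before day 90, so that the late side of the window adds nothing to the endpoint.
3. Use one time origin in Table 1, Study assessments and follow-up, and Primary outcome, and apply it to mortality as well. Randomization is the simplest choice because T4 is already counted from it.

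Cost: the trial is recruiting (Trial status), and amendments go to the ethics committees and competent authorities (Trial ethics and governance), so this is more than an edit. Some contacts will take place slightly later. No visit is added, and the sample size of 175 per group is unchanged. For patients already contacted before day 90, the missing days can be recovered only by a further contact.
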